### Sample size

The sample sizes of Part 1 and 2 depend on each other. To demonstrate an effect size in Part 2 of 5 points on the HADS as statistically significant, anticipating a standard deviation of 11 (i.e. two times the baseline standard deviation of the HADS), 77 participants in each condition are needed at follow-up (power 80%, significance level 5%). Anticipating a drop-out rate of 25% between baseline and 6 month follow-up, 103 participants per condition, thus 206 in total, need to be included at baseline. Estimating a willingness to participate in this RCT of 60%, 343 patients will need to be approached to participate in the RCT in Part 2 [49]. Taking into account a prevalence rate of adjustment disorders of 11% as estimated by Mehnert et al. [7], 3119 cancer patients need to be screened in Part 1 to identify 343 patients with adjustment disorders. Anticipating a response rate of 50%, 6238 patients need to be approached for the screening.

### Statistical analysis

In Part 1 and Part 2 quantitative analyses will be performed using the IBM Statistical package for the Social Science (SPSS) version 25 (IBM Corp., Armonk, NY USA) and STATA version 14 Descriptive statistics will be generated for all socio-demographic and clinical characteristics and outcome measures. Chi-square tests, independent t-tests and Mann-Whitney tests (in case of non-normality of the measure) will be used to analyse whether randomization resulted in comparable patient groups. Analyses will be performed according to the intention-to-treat principle. A *p*-value < 0.05 will be considered significant.

Part 1 aims to investigate the prevalence of having an adjustment disorder, to investigate the uptake of psychological treatment among cancer patients with an adjustment disorder and to investigate its determinants. Determinants of having an adjustment disorder or uptake of psychological care will be entered one-by-one to the logistic regression model using a p-value for entry of 0.05. Potential determinants include scores on the patient-reported outcomes, socio-demographic, and clinical characteristics of the patient, as well as HCP characteristics. Part 2 aims to investigate the effectiveness of the intervention on the primary outcome measure (HADS) with the use of linear mixed models. The linear mixed model will contain a fixed effect for arm/group, time and their two-way interaction, and a random effect for subject. A significant (*p* < 0.05) two-way interaction indicates a difference in effectiveness between the intervention and the control group. In that case, post-hoc effect sizes, at 3 and 6 months follow-up, will be calculated using Cohen’s d.

For the cost-utility analyses, pertinent guidelines will be used [44]. Analyses will be conducted in agreement with the intention-to-treat principle from both a societal and healthcare perspective. Costs will be calculated by multiplying resource use by integral cost prices as presented in the cost guideline [44]. Productivity losses due to absenteeism and presenteeism will be calculated using the friction cost approach. Missing data on costs and utilities will be imputed using multiple imputation. The time horizon will be set at 6 months, and therefore neither costs nor effects need to be discounted. Incremental cost-utility ratios (ICURs) will be calculated with their 95% confidence intervals using 5000 bootstrap replications, which will be projected on a cost-utility plane. In addition, ICUR acceptability curves will be presented and sensitivity analyses will be performed focusing on uncertainty surrounding most important cost items.

For the budget impact analyses, the current guideline on budget impact analyses of the Dutch National health Care Institute (ZIN) and the International Society for Pharmacoeconomic and Outcomes Research will be used [44, 50]. To perform a budget impact analysis insight is needed on: a) size of the target population, b) costs of the intervention and 3) other costs (such as other healthcare costs). Several budget impact analyses will be performed, as this will provide insight into the uncertainty surrounding the budget impact of providing psychological treatment to patients with cancer with an adjustment disorder. Budget impact analyses will be performed from a healthcare (i.e. including intervention costs and healthcare costs), societal (i.e. including intervention costs, healthcare costs, costs of the patient and his/her family and costs in other sectors) and insurer perspective (i.e. including costs reimbursed by the healthcare insurance company).

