Second, patients with an increased risk for an adjustment disorder (i.e. HADS score > =11, DT > =4 or work/school/study problems, family or social problems, emotional problems, fatigue or wanting to talk to a psychologist or social worker as reported on the problem list) will be invited for a diagnostic interview by a registered psychologist, psychotherapist or psychiatrist trained in clinical care for cancer patients with an adjustment disorder (further called healthcare professional (HCP)). During this diagnostic interview by telephone or face to face the presence of an adjustment disorder will be investigated. HCPs will follow the Dutch guideline on adjustment disorder diagnosis [36]. The guideline committee recently defined adjustment disorder in patients with cancer as the combination and interaction among three pillars, namely stressors (e.g. cancer diagnosis, fear of cancer recurrence, physical changes in a patients’ appearance), insufficient protective factors (e.g. resilience, physical health, meaning, social support, autonomy), and the experience of symptoms (e.g. anxiety, depression, fatigue, relation problems, limited work productivity) [3]. During the diagnostic interview, the HCP will also complete a form on sociodemographic (age, gender) and clinical (tumour site, stage, phase of cancer (acute/chronic/palliative), time since diagnosis, treatment modality) parameters, and a form on stressors experienced, protective factors, symptoms experienced and actual psychologic diagnosis. To monitor the robustness of this diagnosis, the diagnostic interview will be audio recorded in case the patient provides specific informed consent on this matter. Approximately 5 % of the total diagnostic interviews will be scored twice (adjustment disorder yes/no).

Additionally, all participating HCPs will be asked to complete a questionnaire on type of care (primary or secondary care), profession and training, and years of experience in working with cancer patients.

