## Discussion

This paper describes the protocol of a study that aims to provide evidence on the prevalence of an adjustment disorder among cancer patients and the reach, effectiveness, cost-utility and budget impact of tailored psychological treatment.

The first part of this project aims to investigate the prevalence. As mentioned above, previous studies have found prevalence rates varying between 6 and 19% [5–8]. However, these studies were heterogeneous in terms of cancer type and methodological quality, warranting further research. Also, the conceptualization of adjustment disorder among cancer patients is poorly studied, which may limit the precision of adjustment disorder diagnosis [51]. Most studies used diagnostic interviews to diagnose adjustment disorder [5–8]. Mehnert et al. [7], on the other hand, first screened patients on their level of psychological distress using the patient health questionnaire (score of 9 or higher on the PHQ-9), followed by a diagnostic interview in those patients with increased levels of psychological distress. As it is estimated not to be feasible to conduct a diagnostic interview in the more than 3000 patients needed for this study, we will in line with the study of Mehnert et al. [7] first screen the patients on their risk for having an adjustment diagnosis using patient-reported outcomes measures. As it is not yet clear which screening questionnaire should be used to preselect patients on their risk for having an adjustment disorder [3], we will preselect patients using the DT, problem list and the HADS. Previous studies have investigated the predictive value of the DT [52–54], HADS [53, 55–59], PHQ-2 [52], Zung Self-rating Depression Scale (ZSDS) [60] and One Question Interview (OQI) [54] to identify patients with an adjustment disorder. Most studies, however, have been conducted on the HADS and DT. Three studies that investigated the predictive value of the DT showed that a cut-off ranging between the > 3 and > 5 resulted in the best screening performance, whereas other studies investigating the HADS found a cut-off ranging between > 9 and > 15. In our study all patients with an increased risk on the questionnaire (i.e. HADS score > =11, DT > =4, certain problems on the problem list or wanting to talk to a psychologist or social worker) will be asked to participate in the diagnostic interview. In line with the study of Mehnert et al. [7], we expect to find a prevalence rate of adjustment disorder of 11% (independent of other diagnoses).

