### Strengths and limitations

A strength of this study is that its design is in line with clinical practice, as we will investigate a tailored psychological intervention, which may consist of different types of interventions, and not only one specific intervention. Second, this study investigates not only the effectiveness and cost-utility of tailored psychological treatment, but also the prevalence of adjustment disorder and reach of the tailored care. Insight in the prevalence and reach will enable accurate budget impact analysis of providing such psychological treatment to cancer patients with an adjustment disorder. Third, the proposed study will assess the cost-utility and budget impact of the intervention from a healthcare, societal and insurer perspective. So far, the majority of the performed economic evaluations have used the healthcare perspective. However, several guidelines recommend using the societal perspective which includes also for examples productivity losses and informal care costs [61, 62]. This is of importance since these costs have shown to be a great contributor to costs of cancer [63]. Finally, detailed analysis will be conducted on determinants of the prevalence of an adjustment disorder and the reach of psychological care, which will help to identify possible risk groups in the future.

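### HADS, distress thermometer and problem-list scores decide who is interviewed, yet they are also candidate determinants of having an adjustment disorder; such associations would arise partly by construction or hold only given a positive screen.

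*Protocol article*

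**What the plan says.** All statements are in the protocol article.

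- **Candidates.** Statistical analysis, on having an adjustment disorder or taking up psychological care: "Potential determinants include scores on the patient-reported outcomes, socio-demographic, and clinical characteristics of the patient, as well as HCP characteristics".
- **Entry rule.** The determinants "will be entered one-by-one to the logistic regression model using a p-value for entry of 0.05".
- **Who is interviewed.** Part 1: prevalence and reach sets the criteria for increased risk: "HADS score > =11, DT > =4 or work/school/study problems, family or social problems, emotional problems, fatigue", or a wish to talk to a psychologist or social worker. Patients meeting any of these "will be invited for a diagnostic interview by a registered psychologist, psychotherapist or psychiatrist". No interview of screen-negative patients is described.
- **The screeners count as patient-reported outcomes.** In the Discussion the authors say they will "first screen the patients on their risk for having an adjustment diagnosis using patient-reported outcomes measures".
- **Outcome definition.** Table 1 gives the screening set (DT, problem list, HADS) together with the interview as the instrument for adjustment disorder yes/no.
- **Denominator.** Sample size counts prevalence over everyone screened: 343 cases among 3119.
- **Purpose.** Strengths and limitations presents the determinants analysis as one "which will help to identify possible risk groups in the future".

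No section removes the screening scores from the candidates for the diagnosis outcome, and none names the patients in whom that model is fitted.

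**The concern.** A variable that controls whether the outcome can be observed is a poor candidate for explaining it. A screen-negative patient has no route to a recorded diagnosis, so a higher HADS or DT score, or a ticked problem, raises the chance of a diagnosis even if it has nothing to do with the disorder. Leaving out the screen-negatives removes that mechanism. But the model then describes patients selected on these same scores, and its odds ratios answer a narrower question than who among cancer patients is at risk.

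The symptom component of the diagnosis also includes anxiety, depression and fatigue, so the scores overlap with the outcome in either set.

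The study was requested to inform reimbursement, and this analysis is offered as a way to find risk groups. A reader could take features of the screening rule for risk factors.

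**Working it through.** **The plan's own figure.** The determinants model has no stated figure. The prevalence denominator reproduces: 343 / 0.11 = 3118.2 (stated as 3119), that is, cases over all screened patients. If the determinants model uses the same denominator, screen-negatives enter as having no disorder.

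**A. All screened patients, worst case.** Assumptions, not from the documents: criterion X is present in 40% of patients; a share q meets some other criterion; the disorder is independent of all criteria, with true prevalence 15%.
- P(diagnosed | X present) = 0.15, because all are interviewed. Odds = 0.15/0.85 = 0.1765.
- P(diagnosed | X absent) = 0.15 × q.
- q = 40%: 0.06; odds 0.06/0.94 = 0.0638; odds ratio 0.1765/0.0638 = 2.76.
- q = 60%: 0.09; odds 0.09/0.91 = 0.0989; odds ratio 1.78.
- With the plan's 11% as true prevalence: (0.11/0.89)/(0.044/0.956) = 2.69 and (0.11/0.89)/(0.066/0.934) = 1.75.

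The true odds ratio is 1 throughout. This is a worst case because the screen then misses 0.6 × 0.6 = 36% of cases at q = 40% and 0.6 × 0.4 = 24% at q = 60%.

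**B. All screened patients, a screen that misses few cases.** Assumptions: prevalence 11%; X present in 40% of patients and 60% of cases; 5% of all cases missed, necessarily among those without X.
- P(disorder | X present) = 0.11 × 0.60/0.40 = 0.165; odds 0.1976.
- True P(disorder | X absent) = 0.11 × 0.40/0.60 = 0.0733; odds 0.0791; true odds ratio 2.50.
- Recorded P(disorder | X absent) = 0.11 × 0.35/0.60 = 0.0642; odds 0.0686; observed odds ratio 2.88.
- Inflation = 2.88/2.50 = 1.15, about 15%.

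**C. Simulation with correlated scores.** 3119 screened patients; disorder rate 11%, independent of every score; problem-item endorsement 20–60%; correlation between scores 0.3–0.6; 50–76% screen-positive; 200 replications for each of six scenarios. The score distributions are assumptions.

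| Set analysed | p < 0.05 | Median odds ratios (true value 1) |
|---|---|---|
| All screened, negatives coded 'no' | 98–100% | 1.29–1.95 per 5.5 HADS points; 1.12–1.36 per DT point; 2.25–5.35 for the problem item |
| Interviewed only | 3–8% | 0.99–1.02 |

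**D. Interviewed patients only, when one criterion truly matters.** Result C for interviewed patients holds when no score is related to the disorder. Now let X (40%) be unrelated, and let another criterion Y, independent of X, have a true odds ratio of 2 to 5, at overall prevalence 15%. Interviewed patients without X all have Y, so the unadjusted odds ratio for X is odds(0.15) / odds(P(disorder | Y present)).
- Y in 40%, odds ratio 2: P(disorder | Y present) = 0.204, odds 0.257; X gets 0.1765/0.257 = 0.69.
- Y in 40%, odds ratio 5: 0.271, odds 0.372; X gets 0.47.
- Y in 60%: X gets 0.79 (odds ratio 2) to 0.64 (odds ratio 5).

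Entered singly, an irrelevant criterion looks protective. With adjustment for Y it returns to 1, since among patients with Y the disorder does not depend on X.

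**The case against.** The strongest reply is that the Statistical analysis section names no analysis set, so the construction artefact is not established. Listing healthcare professional (HCP) characteristics, which attach to a patient through the interview, points at least as much to a model in interviewed patients. There the simulation shows no artefact when nothing is related to the disorder, and adjustment for all screening criteria removes the distortion in step D. This stands. A reader might infer that the plan as written must report its own screening rule as the leading determinants; the article does not support that.

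Other stronger readings also fail:

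- **An odds ratio of 2.8 as the expected size.** It requires a screen unrelated to the disorder. The Discussion cites work on the predictive value of the HADS and DT, and the any-of rule is broad, so the bias is probably smaller.
- **That one model cannot hold both patient scores and HCP characteristics.** It can, among interviewed patients, who have both.
- **That the Checklist Individual Strength (CIS) is affected in the same way.** It is collected alongside the screeners but does not decide who is interviewed. Only symptom overlap applies.
- **That entry "entered one-by-one to the logistic regression model using a p-value for entry of 0.05" is an error.** For an exploratory analysis this is largely a matter of preference. The article gives no number of candidates from which to compute a false-selection rate.

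What the reply leaves standing: the candidate list is a stated choice, the screening scores are within it, and neither possible set lets them be read as risk factors for cancer patients in general.

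**Conclusion.** The concern holds in a conditional form. The protocol article offers, as determinants of having an adjustment disorder, scores that also control access to the diagnosis.

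- **If screen-negatives are counted as having no disorder**, as in the prevalence denominator, the associations are inflated by design. The illustrations run from about 15% (5% of cases missed) to an odds ratio of 2.76 for an unrelated item (36% missed). The direction follows from the design; the size depends on the assumed sensitivity and score distributions, which the article does not give.
- **If only interviewed patients are analysed**, the associations are conditional on a positive screen. Without adjustment for the screening criteria, an unrelated item can look protective (0.47 to 0.79 under the assumptions shown).

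The point is confined to the Part 1 model for having the disorder. The uptake model concerns diagnosed patients and is unaffected, as is Part 2.

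**What to change.** For the outcome of having an adjustment disorder:

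1. Remove the HADS, the DT and the problem-list items used for screening from the candidate determinants, and use socio-demographic and clinical variables. Alternatively, fit the scores only among interviewed patients, adjusted for the screening criteria, and report them as correlates of diagnosis given a positive screen, not as risk factors.
2. Fit HCP characteristics only among interviewed patients.
3. State the analysis set of each model. Where screen-negatives are included, say that they are assumed, not verified, to be free of the disorder. This caveat also matters for the remaining variables, since any that is related to screening positive can carry some of the same bias.
4. Add a caveat about symptom overlap if the CIS is kept as a candidate for this outcome.

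The patient-reported scores, including the CIS, may stay as candidates for uptake among diagnosed patients.

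The cost is a few sentences of analysis text and no new data. The downside is that screening scores can no longer be presented as risk factors for the diagnosis.

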### Part 2: randomization

Randomization will be conducted centrally by an independent person in blocks of four and six using an automatically created randomisation list. Randomization will be stratified for the patient self-reported prognosis and severity of psychological distress by an independent person. Patients are not blinded to treatment allocation. Data managers will be blinded to the treatment allocation.

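### The primary mixed model gives each arm its own baseline HADS mean and leaves out the randomisation strata: an unbiased but avoidably less efficient analysis that does not match the sample-size calculation

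*Protocol article*

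**What the plan says.** The Statistical analysis section of the protocol article sets out the primary model: "The linear mixed model will contain a fixed effect for arm/group, time and their two-way interaction, and a random effect for subject". A significant interaction is the criterion for effectiveness, and effect sizes at 3 and 6 months are calculated only if it is significant. T0 is completed before randomisation and is followed by assessments at 3 and 6 months (Part 2: study population and inclusion procedure). No baseline covariate and no common-baseline constraint is stated.

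Part 2: randomization adds: "Randomization will be stratified for the patient self-reported prognosis and severity of psychological distress". Neither factor is in the stated model.

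The Sample size section aims at an "effect size in Part 2 of 5 points on the HADS", "anticipating a standard deviation of 11 (i.e. two times the baseline standard deviation of the HADS"), from which "77 participants in each condition are needed at follow-up". It gives no correlation between baseline and follow-up, and does not say whether 11 is the SD of a follow-up score or of a change.

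**The concern.** Because T0 precedes randomisation, the two arms have the same expected baseline mean. A model that still estimates a separate baseline mean per arm turns the treatment effect into a difference in change from T0, and so carries the chance baseline imbalance into the estimate with a coefficient of 1. A baseline-adjusted model, or one with a common baseline mean, lets the data set that coefficient.

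Two things are at stake. The first is precision: the change contrast can need more patients than the adjusted one for the same power. The second is agreement within the plan: the sample size rests on one contrast and the primary test on another, with no correlation given to link them. The model also ignores the factors used to randomise, one of which (severity of distress) is close to the primary outcome itself.

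**Working it through.** **Inputs.** From the Sample size section: difference 5, SD 11 (so baseline SD 11/2 = 5.5), 80% power, 5% significance, 77 per arm at follow-up. The baseline to follow-up correlation ρ is not in the document; it is an assumption and is varied. Complete data on 77 per arm are assumed.

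**Reproducing the stated number.** n = 2(1.960 + 0.842)² × 11² / 5² = 2 × 7.849 × 121 / 25 = 75.98, so 76 by the normal approximation. The t-test gives 76.95, so 77, as stated. A one-sided test would give 60, so the calculation is two-sided. Power at 77 is 80.5% (normal) or 80.0% (t). Then 77/0.75 = 102.7, so 103 per arm and 206 in total. The figure is thus a comparison of one value per patient with SD 11. No correlation enters it.

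**The two contrasts.** With baseline SD s0 and follow-up SD s1, the variance per patient is:

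- planned (change): s0² + s1² − 2ρ·s0·s1
- baseline-adjusted or common baseline: s1²(1 − ρ²)

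The first minus the second is (s0 − ρ·s1)², which is never negative and is zero only when ρ = s0/s1. With equal SDs the ratio of adjusted to planned variance is (1 − ρ²)/(2(1 − ρ)) = (1 + ρ)/2.

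Power for the 6-month contrast is Φ(5 / (SD × √(2/77)) − 1.96), with SD the square root of the variance above.

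| ρ | SD 11 at both visits: planned | adjusted | SD 5.5 then 11: planned | adjusted |
|---|---|---|---|---|
| 0.2 | 60.6% | 82.1% | 78.6% | 82.1% |
| 0.25 | 63.4% | 83.0% | 80.5% | 83.0% |
| 0.3 | 66.4% | 84.1% | 82.5% | 84.1% |
| 0.4 | 73.1% | 86.8% | 86.4% | 86.8% |
| 0.5 | 80.5% | 90.3% | 90.3% | 90.3% |
| 0.6 | 88.4% | 94.1% | 93.8% | 94.1% |
| 0.7 | 95.4% | 97.7% | 96.7% | 97.7% |

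With SD 11 at both visits, the variance ratio is 0.65 at ρ 0.3 and 0.75 at ρ 0.5, and the planned power is below 80% for ρ under 0.5. With 5.5 and 11, the planned variance is 151.25 − 121ρ and the adjusted one is 121(1 − ρ²). The ratio is 116.16/127.05 = 0.91 at ρ 0.2, 1.00 at ρ 0.5 and 61.71/66.55 = 0.93 at ρ 0.7. The planned variance equals 121 (SD 11) at ρ = 0.25, so a shortfall needs ρ below about 0.25.

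Two further readings of the SD give no shortfall on this contrast. If 11 is the SD of change, power is 80.5%. If the SD stays at 5.5 at both visits, power is at least 97.9% for any ρ of 0 or more.

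**The interaction test itself.** If time is categorical (its coding is not stated), the interaction has 2 degrees of freedom and its power also depends on the 3-month effect. With SD 11 throughout and ρ 0.5, it is 83.9% if all 5 points are present at 3 months and 71.5% if only 2.5 are. A common baseline mean gives 95.6% and 85.0%. With 5.5 at baseline, 11 afterwards and ρ 0.3, the planned model gives 91.4% and 76.5%, against 93.2% and 79.0%. In that last case most of the loss comes from the joint test and the smaller 3-month effect, not from how baseline is handled.

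**Strata.** The document gives no cut-point for severity, so a median split of baseline HADS was assumed and simulated (4,000 runs, SD 11). With the strata left out, the type I error of the change contrast was 2.5% to 4.0% instead of 5%, which is conservative. At ρ 0.4, power was 74.2% without strata, 81.4% with a stratum-by-time term and 85.9% with baseline adjustment.

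**Covariance.** Suppose the subject effect is a random intercept with independent, equal-variance residuals, and the true correlations are 0.6 (0 to 3 months), 0.4 (0 to 6) and 0.6 (3 to 6). The model then uses 2(1 − 0.533) = 0.933 for the 6-month change where the true value is 2(1 − 0.4) = 1.2. The SE is √(0.933/1.2) = 0.88 of what it should be, and the type I error of that single contrast is 8.4%. Under the same correlations the 3-month contrast is conservative (3.4%), and the 2-degree-of-freedom interaction test stays at about 5.3%.

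**The case against.** The strongest reply is that the stated model is a common longitudinal analysis, gives an unbiased treatment effect under randomisation, and loses little with the SDs that the Sample size section implies: at correlations of 0.3 to 0.5 the gain from adjustment is under 2 percentage points of power. That stands, and it limits the size of the point.

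Four stronger readings are tempting, and the document supports none of them.

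- A reader might infer that the baseline HADS is wasted. It is used, with its coefficient fixed at 1. With SDs of 5.5 and 11 and a correlation of 0.5, that is exactly the best coefficient.
- A reader might infer that the trial falls below 80% power. This takes a correlation under 0.5 together with SD 11 at baseline, although the text makes 11 twice the baseline SD; or a correlation under about 0.25 with the implied SDs; or a smaller 3-month effect under the joint test. The document gives no figure that establishes any of these.
- A reader might infer an inflated type I error from the random intercept. The 8.4% belongs to one contrast under assumed correlations, not to the stated interaction test with categorical time. The article also does not say that the residuals are independent with equal variance.
- A reader might infer that omitting the strata invalidates the test. In the simulation it made the test conservative.

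It can also be said that covariates and covariance structure belong in an analysis plan that is not shown. This holds for the residual covariance. It does not dispose of the main point, because the article lists the fixed effects of the primary model and names the term that decides effectiveness.

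**Conclusion.** The point holds as an efficiency and consistency finding. The stated model tests a change-from-baseline contrast, omits both stratification factors, and differs from the comparison that gave 77 per arm. The adjusted contrast is never less precise, since the variances differ by (s0 − ρ·s1)². The loss runs from nothing to 9% of the variance with SDs of 5.5 and 11 (correlations 0.2 to 0.7), and reaches 35% with SD 11 throughout and a correlation of 0.3.

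These figures rest on assumed correlations, complete data, and a reading of SD 11 that the document leaves open. The strata result rests on an assumed median split. Neither bias nor an inflated type I error is shown for the stated test, and a power shortfall is possible but not established. It is worth correcting because the correction is nearly free, but it is not a must-fix error.

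**What to change.** Before unblinded data are seen, restate the primary model in one of two ways: constrain the two arms to a common mean at T0, or use T0 HADS as a covariate with T1 and T2 as the outcomes. Add self-reported prognosis and severity of distress together with their interactions with time. In a model that keeps separate baseline means, stratum main effects alone would not change the complete-data interaction test.

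An unstructured covariance over the three visits is a sensible companion, because the Sample size section anticipates a larger SD than at baseline. State also whether SD 11 refers to a follow-up score or a change, and which correlation is assumed, so that the sample size and the primary test can be compared.

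The cost is a few sentences and a few lines of code. Every variable needed is already collected before randomisation, and the sample size need not change: for the 6-month contrast with follow-up SD 11, adjusted power at 77 per arm is at least 80.5% whatever the correlation.
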